## 2. Materials and Methods

### 2.1. Study Settings and Design

This semi-randomized controlled trial will compare the level of experience in various aspects of motor control and learning in two Pilates-based skills (standing plank, and the side crisscross. See Appendix A—Figure A1). The study protocol has been approved by the Ethics Committee of the Faculty of Sport and Physical Education at University of Coimbra (number CE/FCDEF-UC/00042022) and was submitted and approved by their Scientific Council. Table 1 summarizes the combination of variables and outcomes that are relevant to our study goals.

The experience level of the participants is an independent variable manipulated through the presence or absence of a mirror during the exercises [25]. This allows control of possible variables that could impact the object of the study. Both Pilates-based exercises also provide a means of controlling for these variables and ensuring that the exercises are unfamiliar to all participants. Environmental factors and organic characteristics of the participants will not be used as they are not relevant to the objective of the study. However, Body Mass Index (BMI) can be considered due to its correlation with strength [26]. These design choices result in suitable statistical analyses using linear or nonlinear methods.

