The influence of Pilates practice on neuro-muscular and cognitive function is interesting to address. Thus, research on physical activity using EEG signals, combined with nonlinear methods, will lead to new horizons in brain function research [14,15]. Recent studies point to advantages to cognitive performance in athletes compared to non-athletes [16], and it will be pertinent to obtain this knowledge in other types of activities and physical activity levels. In fact, new technologies and devices can use EEGs to study simple movements, introducing the possibility of investigating new experimental designs [17,18,19].

The gaze behavior associated with motor imagery obtained from mirror images may provide information regarding the motor control, learning speed and movement quality [20,21,22]. In activities with precise movements, such as dance, Pilates, or martial arts, the impact of the presence of a mirror and the gaze behavior of the practitioners still needs research [23]. Furthermore, the output of quality of movement, particularly if associated with other data, could be very useful for obtaining a clearer glimpse of these phenomena [24].

The objective of this study is to investigate how the Pilates method affects the learning process, motor control, and neuromuscular stabilization of the trunk, specifically in experienced and inexperienced practitioners. Secondly, it aims to identify differences in strength and muscle recruitment among the four selected muscles that we are studying. Finally, we aim to build a pattern or map of brain waves and gaze behavior, which will be created according to the practitioner’s level of experience and length of practice.

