The assessments are made with the subjects in a supine position at rest and using the abdominal hollowing maneuver. Three shear modulus data points will be recorded for each muscle where the average mean is used as the relative value [38]. The system will record the shear wave velocity in meters per second (m/s), the median elasticity in kilopascals (kPa), and the measurements for depth and diameter in centimeters. Additionally, the SWE results can be presented in the form of an elasticity map, where different colors are assigned to represent varying values, creating a heatmap that visualizes the data.

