**Figure 3 healthcare-12-00229-f003:**
[figure not shown]
Figure of marker set placement (adapted from ROBOCORP Laboratory; the image does not require a copyright).

**Table 1 healthcare-12-00229-t001:** Study variables.

Dependent Variables							
			AWMUS + SWE	EEG	GAZE	QUALI	Video *
Independent Variables	Level of experience in Pilates	Control group	S1	S2	S3	S4	-
		Non-expertise group					
		Expertise group					
	Mirror	Mirror image	S1	S2	-	S4	-
		No mirror image					
	DEXA *		-	-	-	-	-

Legend: S1—study 1; S2—study 2; S3—study 1; S4—study 4; ECO—Abdominal Wall Muscle Ultrasound (AWMUS); SWE—Shear Wave Elastography; EEG—Electroencephalography; GAZE—Gaze behavior Assessment; QUALI—Qualitative research; DEXA—Dual-energy X-ray Absorptiometry. * Correlated variables—Used to establish analysis and identification correlations with other variables.

**Table 2 healthcare-12-00229-t002:** Sample operationalization and descriptive data.

Topic	Description	Operationalization	
Age	Age range between 30 and 50 years old		No pathologies that make physical practice unfeasible (according to RGPD and DL nº5/2007)
Gender	Gender Balance (approximately 20 males and 20 females)		
Experience level	Expertise	Practitioners who attend Pilates sessions in one of its forms, for more than 6 months with a frequency equal to or greater than two weekly workouts lasting between 45 and 60 min [27]	
	Non-expert	Practitioners who have never performed Pilates sessions in any of its forms or subjects who have performed Pilates for less than 3 months for more than a year will also be admitted to this group [27].	
Health condition		Unhealthy subjects will not participate in the study according to Portuguese law. The following will exclude participants from the sample: glaucoma, epilepsy, or pregnancy [27]	

**Table 3 healthcare-12-00229-t003:** Markers of anatomical assessment for each muscle [13,31].

Muscle	Anatomical Marker
RA	Measurements on the right side only Probe: Vertical Zone: 10 cm to the left of the umbilical scar at the midpoint between the iliac crest and the last rib
EO	
OI	
TrA	Measurements on the right side only Probe: Horizontal Zone: At the level of the navel and 2 cm to the right of the mid-axillary line

**Table 4 healthcare-12-00229-t004:** Markers of anatomical assessment for each muscle.

Marker Name	Location
RALH	Approximately over the temple and preferably aligned with the lateral commissure of the eye
LALH	

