## Appendix C

**Table A2 healthcare-12-00229-t0A2:** Protocol applied in laboratory (day 1 and 2 until lunch time).

Researcher				Action				
		A	1	Greeting and Welcoming/Informed Consent				
C			2	Ultrasound 1 (at rest)				
	B	A	3	Equip the subject with the apparatus for the study		EEG		
						Video Motion		
						Tobii		
	B		Mirror Protects the massage table					
		A	4	Calibration		EEG (RELAX- Eyes open/Eyes closed)		
						Tobii		
		A	5	Video viewing 1				
	B		Front Mirror Machine					
C	B		6	Ultrasound 2 during exercise 1 Standing plank: ACTION!				
		A	7	Video viewing 2				
	B		8	Side Mirror (LEFT) of the Machine				
	B		9	ACTION—exercise 2—Side Criss Cross				
	B		10	Unequip the participant (thank you message)				
					Batterie		EEG	
			11	Equipment check			Tobii	
		A			SD Card		Tobii	

**Table A3 healthcare-12-00229-t0A3:** Protocol applied in laboratory (day 2 after lunch time and day 3).

Researcher				Action				
		A	1	Reception/Free and Informed Consent				
C			2	Ultrasound 1 (at rest)				
	B	A	3	Equip the subject with the apparatus for the study		EEG		
						Video Motion		
						Tobii		
	B		Mirror Protects the massage table					
		A	4	Calibration		EEG (RELAX- Eyes open/Eyes closed)		
						Tobii		
		A	5	Video viewing 1				
	B		Front Mirror Machine					
C	B		6	Ultrasound 2 during exercise 1 Standing plank: ACTION!				
		A	7	Video viewing 2				
	B		8	Side Mirror (RIGHT) of the Machine				
	B		9	ACTION—exercise 2—Side Criss Cross				
	B		10	Move the machine side mirror (LEFT)				
	B		11	Unequip the participant (thank you message)				
					Batteries		EEG	
			12	Equipment check			Tobii	
		A			SD Card		Tobii

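### Mirror versus no mirror is a declared factor, but both laboratory schedules use a mirror throughout, so its effect cannot be estimated for the standing plank and is undefined for the side crisscross

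*Protocol article*

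**What the plan says.** Section 2.1 of the protocol article introduces the mirror in this sentence: "The experience level of the participants is an independent variable manipulated through the presence or absence of a mirror during the exercises".

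Table 1 sets things out differently. Level of experience and mirror are two independent variables. The mirror variable has two levels, the second being "No mirror image", and it is entered for S1 (the joint column for abdominal wall ultrasound and elastography), S2 (EEG) and S4 (qualitative). The gaze column has a dash.

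Appendix C gives the laboratory steps in two schedules. Table A2 is headed "Protocol applied in laboratory (day 1 and 2 until lunch time" and Table A3 "Protocol applied in laboratory (day 2 after lunch time and day 3" (closing brackets omitted). Each has the step "Front Mirror Machine" before the standing plank, at which the second ultrasound is taken. Each then places a side mirror before the side crisscross: on the left in Table A2, and in Table A3 "Side Mirror (RIGHT) of the Machine". Table A3 adds a move of the side mirror to the left after the crisscross. No step in either table is labelled as being without a mirror.

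On elastography, section 2.4.2 says: "The assessments are made with the subjects in a supine position at rest and using the abdominal hollowing maneuver". Section 2.4.1 has ultrasound thickness measured at rest, during abdominal hollowing, and at the end of the plank repetitions.

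**The concern.** There are two faults. First, the sentence in 2.1 merges two factors. A participant's experience is settled by the eligibility criteria before any session, and a mirror can only be a second, separate condition.

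Second, the procedures do not deliver the second level of that condition. Table 1 promises a mirror comparison in three sub-studies, but the printed steps put a mirror in place for both exercises in both schedules. If staff follow them, there will be no plank data without a mirror, and no analysis can recover a level that was never observed. What does vary, the side of the side mirror, follows the calendar, and the article describes no randomisation or counterbalancing of participants to schedules.

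**Working it through.** **1. The plan's own figure.** Section 2.2 gives a two-tailed test, alpha 0.05, power 90% and d = 1.39. For a two-sample t-test with n per group, the noncentrality is d × √(n/2).

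- n = 11: power 0.873
- n = 12: noncentrality 1.39 × √6 = 3.40, power 0.902
- n = 13: power 0.925

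So 12 per group is the smallest adequate size, and three groups give the 36 of the Abstract. Section 2.2 and the Eligibility Criteria use 13 per group, 39 in all. The calculation rests on one two-group effect size, and no separate figure is given for a mirror contrast.

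**2. The two schedules side by side.**

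| Step | Table A2 | Table A3 |
|---|---|---|
| When used | day 1, day 2 morning | day 2 afternoon, day 3 |
| Mirror for the plank | front | front |
| Ultrasound during the plank | yes | yes |
| Mirror for the crisscross | side, left | side, right |
| Mirror move after the crisscross | none | to the left |
| Step labelled no mirror | none | none |

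**3. Can the plank mirror effect be estimated?** Take 3 × 13 = 39 participants and a model with four columns: intercept, two group indicators, mirror.

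- Mirror present for everyone (as printed): the mirror column equals the intercept; rank 3 of 4; not estimable.
- Mirror and no mirror split within each group: rank 4 of 4; estimable.

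**4. Can the crisscross mirror effect be estimated?** Section 2.4.4 refers to switching sides for bilateral exercises, and section 2.4.5 records EEG per exercise and side. Suppose the side away from the mirror is meant as the no-mirror condition. Let m be the mirror effect and s the left-minus-right difference, and suppose a left mirror serves the left side. The within-person contrast is then

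- Table A2 (mirror left): m + s
- Table A3 (mirror right): m − s

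The mean of the two is m, so the effect can be separated from body side, but only by combining schedules that run on different days. A group seen mostly under one schedule would contribute mostly m + s or mostly m − s. The article states neither the supposition nor who attends when. The extra move in Table A3 comes after the exercise, and no exercise follows it.

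**5. Precision of a repaired plank comparison.** The article gives no split. Assume randomisation within each group of 13 (6 v 7), which gives 19 v 20 overall. With noncentrality d × √(19 × 20/39) = 3.12d:

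- detectable difference at the plan's 90% power: 1.07 SD
- at 80% power: 0.92 SD
- within one group (6 v 7) at d = 1.39: noncentrality 1.39 × √(42/13) = 2.50, power 62%

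For comparison, both conditions in all 39 people would detect 0.46 SD of the paired difference at 80% power. On the outcome scale, multiplying by √(2(1 − r)), this is 0.46 SD at r = 0.5 and 0.46 × √0.6 = 0.36 SD at r = 0.7. Both values of r are assumed.

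**The case against.** **The article is condensed.** Section 2.4 says that each sub-study has its own detailed protocol, and the mirror steps are terse entries in the schedule tables. Condition order and assignment may be set out elsewhere. That stands as a reason not to fault missing detail. It does not remove the conflict, because the article prints step-by-step schedules and these disagree with Table 1.

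**The mirror is not central.** The objectives and expected results concern experience, no mirror hypothesis is stated, and the planned ANOVA with Tukey comparisons is between groups. This stands: the experience comparison does not depend on the mirror contrast.

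A reader might also infer more than the documents support:

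- *That no mirror effect can be estimated at all.* This is shown for the plank only. A contrast of mirror side with other side is possible for the crisscross.
- *That the schedules differ only by calendar day.* They also differ in mirror side and in one step.
- *That mirror presence is confounded with group, or leaks into the expert versus non-expert gaze contrast.* If the mirror is always up, its presence cannot differ between groups. Only day and mirror side could, and the article does not say which groups attend on which day.
- *That gaze must be added to the mirror comparison.* The Introduction's remark that "the impact of the presence of a mirror and the gaze behavior of the practitioners still needs research" is background. Leaving gaze out of that comparison is a choice of scope.
- *That supine elastography will be compared by mirror.* The Table 1 column is joint with ultrasound, which is taken during the plank, so a mirror entry for it makes sense. Table 1 only needs to say which part it covers.

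**Conclusion.** The point holds in limited form. Section 2.1 wrongly describes experience as manipulated by the mirror. Table 1 declares a no-mirror level for S1, S2 and S4 that Tables A2 and A3 do not provide for the standing plank. If the schedules are followed as printed, the plank mirror effect cannot be estimated (rank 3 of 4). The same holds for ultrasound during movement in S1, because the plank is the only exercise with ultrasound during its performance. For the crisscross, estimability depends on an unstated definition of no mirror, and mirror side is tied to day and half-day.

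This rests on reading Tables A2 and A3 as the complete laboratory schedules. The precision figures assume a 19 v 20 split and describe a repaired design, not the size of the fault. The matter should be settled before data collection, since an unobserved condition cannot be restored afterwards.

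**What to change.** 1. Reword 2.1 so that experience (fixed by eligibility) and mirror (set by the investigators) are two separate factors.
2. For the standing plank, either randomise mirror versus no mirror within each of the three groups, show both versions in Appendix C and include mirror in the model, or remove mirror as a factor for the plank outcomes.
3. For the side crisscross, state which side counts as the no-mirror condition, and assign mirror side by randomisation within group instead of by half-day.
4. In Table 1, limit the S1 mirror comparison to ultrasound taken during the plank, excluding supine elastography.

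**Cost.** A randomisation list and moving the mirror between participants, with no added session time. The plank mirror contrast becomes a between-person one that detects only about 1.07 SD at 90% power under the assumed split, and it is weak within a single group. Dropping the factor costs nothing in the laboratory but gives up the plank mirror question. Having each person do the plank both ways would be more precise, but it takes longer and repeats a task chosen to be unfamiliar in a study of learning. Carry-over could differ between experts and novices, and a randomised order alone would not remove that. It is a trade-off for the investigators to weigh, not a requirement.

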#### Eligibility Criteria

The sample for the experienced group will be selected from a local Pilates studio. Participants must have more than six months of practice, with more than 1 h of practice per week [27]. The non-expert group will be composed of subjects who must not have had any Pilates practice in the last three months. For the control group, in addition to not practicing any form of Pilates in the last three months, we also require that they not practice any form of Pilates during the study. These subjects will be allowed to maintain their physical activity routines or create new routines if body and mind activities are not included (yoga, body balance, tai-chi, among others). All groups will be composed of 13 participants between 30 and 50 years of age. The exclusion criteria are pregnancy and medical contraindications to practicing physical exercise [29].

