### 2.6. Statistical Analyses

This study seeks to contribute to the explanation and understanding of phenomena related to Pilates using a mixed quantitative and qualitative methodology. For the statistical treatment and linear analysis, IBM SPSS Statistics 28.0 software (IBM Corporation, New York, NY, USA) will be used, with a level of significance at 5% (*p* < 0.05). Descriptive statistics, including the calculation and analysis of the mean and standard deviation, will be conducted for all variables. If validation of the normality and heterogeneity assumptions of the sample are assured, then the analysis of variance ANOVA [56] will be used with multiple comparisons of means performed using the post-hoc Tukey test to verify the differences between the groups [57]. The effect size (ES) for ANOVA test is interpreted using the following criteria: no effect (ES < 0.04), minimum effect (0.04 ≤ ES < 0.25), moderate effect (0.25 ≤ ES < 0.64), and strong effect (ES ≥ 0.64) [58]. Apart from the effect size, the power (π) of the corresponding test will also be presented [59]. Pearson’s correlation analysis is defined to establish the associations between the studied variables [60].

While linear measures are useful for quantitative data analysis, taking a different perspective, non-linear data analysis is employed to characterize the collected data. This type of analysis provides insights into the organization of data within a system, offering a more nuanced understanding of the underlying patterns and structures in the dataset. The regularity, variability and complexity of the signal and the motor system in different levels of response [61,62] can lead to a larger understanding of the collected data. In fact, sample entropy can tell the amount of uncertainty attending the order of an output signal, i.e., predictability [63]. On the other hand, the Lyapunov exponent will be used to analyze the periodicity and regularity of the signal and the motor system in a time series [61]. Finally, the Hurst exponent [64,65] will be used to measure the tendency of the values of the motor system along a time scale. To proceed with the computation of the time series, the program will use UPATO [66].

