## 3. Results

In general, we anticipate both intra-individual and inter-individual differences that may result in statistically significant variations in the studied variables. This expectation considers the sample’s considerable diversity and variability in terms of morphological characteristics and psychomotor profiles.

Given that we have adopted both linear and non-linear analyses, which will provide a more comprehensive assessment of how the sample has evolved in terms of neuromuscular structures over both space and time, it is expected that the results may exhibit both quantitative and qualitative aspects. This will enable a mixed and more robust analysis of the applied methodology. For instance, within the context of non-linear analysis, we expect that results will show higher entropy in the expert groups when compared to non-experts. Regarding stability, the expert group is expected to exhibit higher Lyapunov exponent values compared to other groups, accompanied by lower Hurst exponent values. In the context of elastography, we anticipate that the elasticity of the transversus abdominis (TrA) muscle will be higher in experienced practitioners compared to those with less experience, both within the same group over time and when comparing across groups.

In terms of gaze behavior, results should reveal a greater number of saccades, more Areas of Interest (AOIs), and less time spent in fixation for the non-expert sample. This is because expert practitioners are assumed to have a more efficient mastery of gaze behavior.

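### Section 2.1 dismisses participants' organic characteristics as irrelevant, contradicts this elsewhere, and leaves the cross-sectional contrasts with a selected expert group open to confounding by sex and body composition

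*Protocol article*

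**What the plan says.** - **Section 2.1, on participant characteristics:** "Environmental factors and organic characteristics of the participants will not be used as they are not relevant to the objective of the study". The sentence that follows reads "However, Body Mass Index (BMI) can be considered due to its correlation with strength". No rule says when or how BMI would enter an analysis.
- **Section 2.1, on design:** "This semi-randomized controlled trial will compare the level of experience in various aspects of motor control and learning".
- **Eligibility Criteria:** "The sample for the experienced group will be selected from a local Pilates studio". Each of the three groups has 13 participants aged 30 to 50.
- **Table 2, on sex:** "Gender Balance (approximately 20 males and 20 females", stated for the sample as a whole.
- **Section 2.4.3 and Table 1:** DEXA yields lean mass, fat mass and bone mineral content. Table 1 lists it among the independent variables with a dash in every study cell. The legend describes such starred variables as "Used to establish analysis and identification correlations with other variables".
- **Section 2.6:** groups are compared by ANOVA with Tukey post-hoc tests, and no covariate is named. Separately, Pearson's "correlation analysis is defined to establish the associations between the studied variables".
- **Section 3:** statistically significant variation is expected, and the reason given is the sample's "considerable diversity and variability in terms of morphological characteristics and psychomotor profiles".

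**The concern.** Experience with Pilates is a status that a person brings to the study. Experts cannot be randomised to it, so nothing in the design makes them resemble the other two groups in sex or build. The Introduction itself lists an excess of women as a limitation of earlier Pilates samples, and an expert group taken from a studio is a likely place for that to recur.

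If muscle thickness or stiffness differs with sex or lean mass, an expert versus non-expert difference in level may partly be a difference in who was recruited. The objective in the Introduction is worded as how the method affects learning, motor control and trunk stabilisation. Section 3 predicts higher TrA elasticity in experts across groups, which is the contrast with the least protection. The data that could help are already being collected, but section 2.1 rules out their use in general terms.

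**Working it through.** **1. The planning figure.** Inputs from section 2.2: d = 1.39, two-sided 0.05, power 90%. For a two-sample t test the noncentrality is d × √(n/2).
- n = 12: 1.39 × √6 = 3.40, power 90.2%, total 36 (the abstract's number).
- n = 13: 1.39 × √6.5 = 3.54, power 92.5%, total 39 (section 2.2's number). A Wilcoxon version, with effective n = 13 × 3/π = 12.4, gives 91.2%, and 12 per group gives 88.7%.

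The sample size is not in dispute. This fixes 13 per group as the base and shows that the calculation is a two-group comparison without covariates.

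**2. The statements side by side.** Organic characteristics are called not relevant. BMI may be considered because it correlates with strength. Morphological diversity is expected to help produce significant variation. The last two cannot both stand with the first.

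**3. Sex.** The article gives neither the sex split per group nor a sex effect, so both are assumed. Bias in a cross-sectional contrast, in within-sex SD, is the sex effect × the difference in the proportion of men. Three splits that each total 20 men, and so satisfy Table 2, are 6/7/7, 4/8/8 and 3/7/10. The table takes the widest contrast in each.

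| Men of 13 | Effect 0.5 SD | Effect 1.0 SD | Effect 1.5 SD |
|---|---|---|---|
| 6 vs 7 (1/13) | 0.04 | 0.08 | 0.12 |
| 4 vs 8 (4/13) | 0.15 | 0.31 | 0.46 |
| 3 vs 10 (7/13) | 0.27 | 0.54 | 0.81 |

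In the 3/7/10 split at 1.0 SD, the other contrasts are 3/13 = 0.23 and 4/13 = 0.31.

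To express this as an observed d, divide by √(1 + effect² × mean of p(1 − p)). For 3 vs 10 at 1.0 SD, p(1 − p) = 0.1775 in both groups, so d = 0.538/√1.1775 = 0.50. With no true group difference, a single unadjusted t test at 13 per group then rejects in 22.9% of trials. For 6 vs 7 at 1.0 SD, d = 0.07 and the rate is 5.3%. Over the whole table d runs from 0.04 to 0.68 and the rate from 5.1% to 38.6%. Tukey adjustment would lower each rate but would not remove the bias.

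**4. A continuous measure such as lean mass.** The shift and the correlation are also assumed. Spurious d = expert shift (SD) × correlation with the outcome. Simulation used 3 × 13 participants, no true effect, 6,000 runs, and an expert contrast at two-sided 5%.

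| Shift, correlation | Spurious d | No covariate rejects | With covariate rejects |
|---|---|---|---|
| 0.5, 0.5 | 0.25 | 10.3% | 5.3% |
| 0.8, 0.5 | 0.40 | 16.8% | 4.8% |
| 1.0, 0.7 | 0.70 | 41.6% | 4.9% |

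**5. Change from baseline.** Ultrasound thickness is taken at the first assessment and after twelve weeks (section 2.4.1). If a stable trait adds the same amount b at both visits, change = (post + b) − (pre + b) = post − pre, and b drops out. The figures in steps 3 and 4 therefore apply to contrasts in level. Change is affected only if the trait alters the response itself.

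**6. Correlations.** If two variables both differ between groups, pooling the groups gives a non-zero correlation even when there is none within groups. The article does not say whether groups are pooled and gives no basis for a size, so none is claimed.

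**The case against.** The strongest reply has four parts.

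- **Stronger readings go too far.** A reader might infer that sex, age and body composition are all declared irrelevant and left out. The sentence names none of the three. BMI is allowed in the next sentence, DEXA has a stated role, age is limited to 30–50, and a sex-balance target exists. In context the sentence may mean only that these characteristics are not experimental factors. This stands against the stronger reading. It does not settle the matter, because neither the age range nor the overall sex target balances groups of 13, and the BMI sentence makes the contradiction plainer.
- **Covariates belong in the analysis plan.** An article need not list them, and their absence from section 2.6 alone would be no finding. But section 2.1 makes a positive statement that they will not be used, and an analysis plan that adjusted for them would contradict it.
- **Repeated measurement protects the comparison.** It does so largely for change. Section 2.6 does not say whether the ANOVA is on change, and section 3 expects differences across groups as well as over time.
- **The imbalances are invented.** They are assumptions. With near-equal sex splits the bias is negligible, which is why the range is shown.

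**Conclusion.** The point holds in a limited form. Section 2.1 is inconsistent with its own next sentence and with section 3, and the cross-sectional expert contrasts are open to confounding by sex and body composition. One might go on to conclude that the expert differences are confounded. The documents do not support that, because they report no imbalance and no effect of sex or build on the outcomes.

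For an assumed 1.0 SD sex effect, the bias runs from about 0.08 SD (6 vs 7 men of 13) to 0.54 SD (3 vs 10), against a planning effect of 1.39. It could weaken or imitate part of an expert difference, but in these scenarios it would not produce one of the planned size. Change from baseline is less exposed. The contradiction in the text rests on no assumption; the size rests wholly on the assumed splits and effects. This should be corrected before the analysis is fixed.

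**What to change.** 1. Delete the sentence in section 2.1 that calls organic characteristics not relevant.
2. Prespecify sex and one DEXA or BMI measure as covariates in the group model, with the baseline value added where the outcome is measured twice.
3. Set the sex-balance target within each group (6 or 7 of each sex in 13).
4. Compute correlations between DEXA and outcomes adjusted for group.
5. Describe expert contrasts as observational associations. Draw effects of Pilates only from non-expert versus control, to the extent that this allocation is randomised.

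**Cost.** Three covariates reduce the error degrees of freedom from 36 to 33. With noncentrality 1.39/√((1 − R²) × (2/13) × variance inflation), power for one contrast at d = 1.39 is:
- 93.2% without covariates;
- 93.0% with three balanced covariates that explain nothing;
- 80.2% at variance inflation 1.5 and R² = 0;
- 90.0% at variance inflation 1.5 and R² = 0.25.

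The loss is therefore small unless the covariates are collinear with group, which is also when adjustment matters most. Balancing sex within groups slows recruitment slightly and limits that collinearity. Adjustment removes only measured confounding; self-selection into Pilates and other activity remain. If long practice itself alters body composition, adjusting for it removes part of what experience contributes, so expert contrasts are best reported with and without the body measure.
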